#### Randomization

Patients will be randomized 1:1 into two groups using a minimization technique with stratification according to center and the number of risk factors for developing diabetes (two or three).Group 1 (interventional group) will be treated with vildagliptin 100 or 50 mg/day for 2 months (depending on whether their glomerular filtration rate is above or below 50 ml/min; Modification of Diet in Renal Disease (MDRD) equation).Group 2 (placebo group) will be treated with placebo according to the same dosage.

Random allocation sequence is generated using CleanWeb™. The minimization algorithm takes into account already randomized patients in order to allocate a new treatment to minimize difference between stratification criteria. The randomization result provided by the system is attributed in 80% of cases; otherwise, the other treatment is attributed. Neither the nurse nor the doctor nor the patient will know the nature of the ingested tablets. The blinding is created by the clinical research associate coordinator. The randomization number is assigned directly to the centers via CleanWeb™.

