### Statistical analysis plan

#### Sample size and power calculation

The estimated proportion of diabetic patients 1 year after transplantation is 40% in group 2 (P_2_) and the expected decrease in group 1 (P_1_) is 50% (i.e., 20% at 1 year) [4, 5]. The expected 50% decrease is estimated according to the results obtained with the insulin treatment of Hecking et al. (100% decrease at 1 year) [6]. With the hypotheses H0 (P_2_ − P_1_ = 0; null hypothesis) and H1 (P_2_ − P_1_ ≠ 0; altenative hypothesis) and by considering a group sequential design with a Z score test (pooled estimate for variance estimation), a bilateral alpha risk of 5% and a ß risk of 20%, it will be necessary to randomize 84 patients per group (a total of 168 patients). We expect 10% of patients at 1 year to be non-evaluable and thus we will include 186 patients in total. An interim analysis is planned by the statistician of the investigation team (without the investor being aware of the lifting of the blind) to reject H0 or H1 when at least 84 patients are randomized with one year of follow-up (42 in each group; 50% of the information fraction) using alpha spending function and O’Brien Fleming boundaries. Sample size calculations were performed with the EAST 6 software.

Moreover, as supportive analysis with this sample size will be able to demonstrate an improvement in the time of diabetes-free occurrence from 40% to 20% (hazard ratio of 0.43) with a bilateral alpha risk of 5% and we will have 90% statistical power with 63 events.

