#### Secondary outcome, exploratory, and sensitivity analyses

Selected efficacy analyses will be repeated in the per protocol population (i.e., subset of the ITT population meeting the following criteria: all eligibility criteria fulfilled, at least one dose of allocated treatment administered). The safety population will be used for reporting the safety and treatment exposure data. A modified ITT population will be used for HRQoL analysis, considering all randomized patients with at least the baseline HRQoL questionnaire available. Continuous variables will be summarized using descriptive statistics, i.e., the number of patients with available data (n), mean, median, standard deviation (SD), 25–75% quartile (Q1–Q3), minimum, and maximum. Continuous variables could be transformed to categorical variables using the median or using conventional cut-offs from bibliography or clinical practice. Frequencies in tables will be presented by arm, total frequency, percentages, and missing modality. Qualitative variables will be summarized by means of counts and percentages. Unless otherwise stated, the calculation of proportions will be based on the sample size of the population of interest. The rate of incidence of NODAT will be determined using confidence interval (CI) and compared using Chi 2 test. Univariate and multivariate logistic analyses will be done to identify the independent prognostic factor of the rate of incidence of NODAT and to compute the odds ratio with 95% CI. The continuous variables will be treated as quantitative and qualitative data using cut-offs in anticipation of elaborating a practical clinical tool. Factors will be considered for inclusion in the model if the univariate p value is ≤ 0.1. Interactions between treatment and some variables will be tested at a two-sided 10% level (i.e., a p value > 0.1 indicates no evidence of heterogeneity of treatment effect across the subgroups for each factor). All tests will be performed in an exploratory purpose at a two-sided 5% significance level.

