##### Health-related quality of life

The minimal clinically important difference will be fixed to 10 points for each HRQoL score. A descriptive analysis of the scores obtained for each questionnaire at baseline and at each follow-up will be performed using n, mean (SD), and median (range) for all patients and according to the treatment arm. A linear mixed model for repeated measure will be applied to HRQoL scores integrating all measurement times, including a treatment effect, a time effect, and an interaction between time and treatment. The time to HRQoL score deterioration (TTD) approach will also be explored. The TTD will be defined as the time from inclusion in the study to the first deterioration of at least 10 points of the HRQoL score compared to the baseline score [13, 14]. The TTD will be determined according to the Kaplan-Meier estimation method and compared by treatment arm using the Log-rank test. Univariate and multivariate Cox regression models will be performed in order to estimate hazard ratio with 95% CI to investigate potential factors independently associated with the TDD.

All tests in HRQoL analyses will be performed at a two-sided 1% significance level to prevent inflation of the alpha type one error with a Bonferroni approach for the five targeted dimensions (5%/5 = 1%; physical health, mental health, medical care and satisfaction, treatment, and fear of losing the graft).

The EQ-5D questionnaire is a standardized tool consisting of five dimensions: mobility, self-care, usual activity, pain and discomfort, and anxiety and/or depression. Each patient’s quality-adjusted life year will be calculated, from D0 until M12 or censoring date, by multiplying the duration of each period by the corresponding period’s utility score.

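### The five HRQoL dimensions are tested by single-step Bonferroni at 1% each; this is valid, but Holm's step-down version is never less powerful at the same 5% family error

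*Protocol article*

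**What the plan says.** The Health-related quality of life subsection of the protocol article sets one threshold for everything in it: "All tests in HRQoL analyses will be performed at a two-sided 1% significance level to prevent inflation of the alpha type one error". It names the method, "with a Bonferroni approach for the five targeted dimensions", and shows the division and the family: "5%/5 = 1%; physical health, mental health, medical care and satisfaction, treatment, and fear of losing the graft".

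The same subsection lists several analyses per dimension: a linear mixed model with treatment, time and time-by-treatment terms, then a time-to-deterioration analysis ("The time to HRQoL score deterioration (TTD) approach will also be explored") with log-rank and Cox models. It does not say which of these carries the conclusion for a dimension. Cox hazard ratios are to be reported with 95% confidence intervals.

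On scale and population it says: "The minimal clinically important difference will be fixed to 10 points for each HRQoL score". The parent section adds: "A modified ITT population will be used for HRQoL analysis, considering all randomized patients with at least the baseline HRQoL questionnaire available". The size of that population is not given, nor is an SD for any HRQoL score. The parent section describes its tests as exploratory at a two-sided 5% level, so the 1% rule is a deliberate tightening for HRQoL. The opening of the Statistical analysis section leaves an HRQoL analysis plan to be approved before the database is frozen.

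**The concern.** Under the stated rule each dimension must reach p ≤ 0.01 even when other dimensions have already been rejected. The purpose given is control of the type I error over five dimensions at 5% in total. Holm's procedure serves that purpose equally well and relaxes the threshold step by step as dimensions are rejected. Where two procedures give the same guarantee and one never rejects less, choosing the other gives up power for nothing, unless it brings another benefit that the plan uses.

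At stake is the number of dimensions on which a real difference is declared, once at least one has been shown. The loss grows with the number of dimensions that the treatment truly affects.

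**Working it through.** **1. The plan's own figure.** 5%/5 = 1%, as stated. Summed over five tests, 5 × 0.01 = 0.05; for independent tests the family error is 1 − 0.99⁵ = 0.0490. The rule does what it claims for one test per dimension.

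**2. Holm's thresholds.** The k-th smallest p value is compared with 0.05/(5 − k + 1), which gives 0.05/5 = 1%, 0.05/4 = 1.25%, 0.05/3 = 1.67%, 0.05/2 = 2.5% and 0.05/1 = 5%. Testing stops at the first failure.

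**3. Why the 5% bound is kept.** Suppose m of the five null hypotheses are true. When Holm first rejects a true one, at most 5 − m false ones have gone before, so the threshold in use is at most 0.05/m. The chance that any of the m true nulls has p ≤ 0.05/m is at most m × 0.05/m = 0.05, whatever the correlation.

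**4. Why Holm never rejects less.** Every Holm threshold is at least 1%, so every p ≤ 0.01 passes. If no p value is ≤ 0.01, Holm stops at its first step. The probability of at least one rejection is therefore identical under both rules.

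**5. Size of the gain.**

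Inputs:
- 84 per arm, from Sample size and power calculation ("it will be necessary to randomize 84 patients per group (a total of 168 patients"). This is the primary-endpoint number, used here for illustration.
- 1:1 allocation, from Randomization.
- A 10-point difference, equal to the plan's minimal important difference. Differences of 4 and 2 points are assumptions.
- SD 20 to 25 and correlation 0.3 to 0.5 between dimensions. Both are assumptions.

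The mean of each test statistic is difference/(SD × √(2/84)). For 10 points this is 10/(20 × 0.1543) = 3.24 at SD 20 and 10/(25 × 0.1543) = 2.59 at SD 25. At a fixed two-sided 1% level, power is about 75% and 51%.

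The two rules were compared by simulating five correlated normal statistics (400,000 replicates per setting). Average power per truly affected dimension:

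| Scenario | SD | Fixed 1% | Holm | Gain (points) |
|---|---|---|---|---|
| All five differ by 10 | 20 | 75% | 84–85% | 9–10 |
| All five differ by 10 | 25 | 51% | 60% | 9–10 |
| Three differ by 10 | 20 | 75% | 78% | 3–4 |
| Three differ by 10 | 25 | 51% | 54% | 3–4 |
| One differs by 10 | 20 or 25 | 75% or 51% | same | under 0.1 |
| All five differ by 4 | 20 | 10% | 11–12% | 1.4–1.9 |
| All five differ by 4 | 25 | 6% | 7% | 0.7–1.1 |
| All five differ by 2 | 20 or 25 | 2–3% | 2–3% | 0.1–0.4 |

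In no replicate did the fixed rule reject where Holm did not. Simulated family error under Holm was 4.2% to 4.6% with no true effect, and at most 4.5% when one, two or three dimensions were affected. With independent dimensions it reached 4.9%, still within the bound.

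**The case against.** Most of the case against making much of this stands.

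- **Nothing is wrong in the plan.** Bonferroni is valid, the division is correct, and a simple conservative rule for secondary patient-reported scores is common. A reader might infer that the HRQoL error rate is miscalculated or uncontrolled across the five dimensions; step 1 of the working shows that it is not.
- **The large gains need an effect the plan never predicts.** A reader might infer that this trial would gain 9 to 10 points of power per dimension. The 10 points are a minimal important difference and a within-patient deterioration threshold, not an expected difference between arm means. The expected primary effect is 40% against 20%, so about 20% of patients would avoid diabetes. If HRQoL benefit came only through that route, a 10-point mean difference would need 10/0.20 = 50 points per avoided case, on every dimension. If an avoided case were worth 20 points (an assumption), the mean difference would be 20 × 0.20 = 4 points and the gain about 1 to 2 points. If it were worth 10, the mean difference would be 2 points and the gain under 0.5.
- **The change is not wholly free.** Holm needs one p value per dimension, and the 1% rule covers all HRQoL tests without naming a leading one. A fixed threshold can be applied to each test as written; Holm cannot until one test is designated.
- **Bonferroni has simple matching simultaneous intervals** (99% each) and Holm does not. The plan reports 95% intervals for the hazard ratios, so it does not draw on that advantage.

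What does not stand is that the exploratory label settles the matter. The subsection departs from the 5% level of its parent section expressly to control the type I error. Once that control is chosen, the step-down form provides it with no less power.

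**Conclusion.** The point holds as a minor efficiency improvement. The fixed 1% rule is valid and is uniformly no more powerful than Holm at the same 5% family error. That ordering depends on no assumption about SD, sample size or correlation.

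The size of the gain does depend on them. It ranges from almost nothing, when one dimension is affected or differences are about 2 points, to 9 to 10 percentage points of average power per dimension in the most favourable case tabulated. The SDs and correlations are assumed because the article gives neither, and 84 per arm may not be the size of the HRQoL population. HRQoL is a secondary outcome, and the primary conclusion does not depend on this choice.

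**What to change.** In the HRQoL analysis plan, before the database is frozen:

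1. Name one treatment test per ReTransQoL dimension, for example the mixed-model treatment test or the time-by-treatment test.
2. Order the five p values and compare them in turn with 1%, 1.25%, 1.67%, 2.5% and 5%, stopping at the first that fails.
3. State that the remaining HRQoL tests (other model terms, log-rank, Cox) are exploratory and outside this family.

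The cost is the choice of one leading test per dimension, a few sentences of text, and the loss of simple simultaneous intervals that match the test decisions. No patients, data or additional alpha are needed. If the team prefers to keep Bonferroni for those intervals, that is defensible, but the intervals reported should then be at the 99% level.

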##### Pharmacoeconomic impact

The total number of NODAT in the early post-transplant period avoided and the total number of acute rejections avoided will be used as the measure of effectiveness. Because effectiveness and direct medical costs will be measured over a period of one year, discounting will not apply to clinical and economic parameters according to recommendations of the Department of Economics and Public Health Assessment of the French Haute Autorité de Santé [15]. The incremental cost-effectiveness ratio will be calculated comparing both interventions using the formula: (Cost group 1 − Cost group 2)/(Effectiveness group 1 − Effectiveness group 2). The robustness of the cost-effectiveness analysis (CEA) will be assessed through only deterministic sensitivity analyses. Different one-way univariate, deterministic sensitivity analyses will performed for parameters likely to influence the results of the CEA.

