### Health economics analysis

The additional cost associated with NODAT could be significantly reduced by efficient prevention. A USA study found that, for the period between 1994 and 1998, a newly diagnosed diabetic patient cost $21,500 in medical expenses 2 years after transplantation [32]. The increase in cardiovascular diseases due to post-transplantation diabetes may account for this additional cost.

The purpose of this health economics analysis will be to investigate the cost-effectiveness of prevention of diabetes with vildagliptin in patients included in the PRODIG clinical trial. The CEA will be performed on resources and effectiveness collected prospectively and aggregated from all patients included in the PRODIG clinical trial. The analysis will be performed from a health care payer perspective. Only direct medical costs will be computed from the inclusion visit of a patient (D0) until the last visit (M12) (i.e. 1-year-long time horizon) [15]. They will include medication (as preventive treatment of diabetes and kidney transplant rejection, lipid-lowering therapy, diabetes treatment, treatment of diabetes and renal transplant complications, treatment of adverse event), hospitalization (complications related to the kidney transplant and/or new diabetes, serious adverse event management, follow-up), inpatient and outpatient consultations, biomedical analyses (glomerular filtration rate, OGTT, Hba1c, proteinuria, serology for human immunodeficiency virus, hepatitis B and C viruses, CMV), and transport. Minor costs and costs considered to be independent of the treatment arm will not be taken into account; nor will indirect medical and intangible costs. Costs will be expressed in Euros (€; reference year 2018). Each cost will be calculated using the official tariff, as, for example, for each hospitalization, the national health-insurance provider’s tariffs for Diagnosis-Related Group.

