Furthermore, health utility-based measures of quality of life are recommended by some decision makers in health care. No studies have addressed changes in utility in patients with the same profile as patients included in the PRODIG clinical trial. The purpose of this secondary analysis will be to assess the association of change in health utility with changes in other variables such as complications or treatment. Some preference-based measures of health status have been developed to facilitate the use of utilities in economic analyses. The EQ-5D is one of the most widely used descriptive systems for health state, recommended by the National Institute for Health Care and Excellence in the UK for the incorporation of health benefits in cost-utility analysis and for which validated preference-based scores are available in France [20–22, 30].

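### Acute rejections avoided is used as a denominator of the cost-effectiveness ratio with no stated effect on rejection, and deterministic-only sensitivity analyses would hide how unstable that ratio may be

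*Protocol article*

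**What the plan says.** Four parts of the protocol article bear on this.

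- **Pharmacoeconomic impact** names two counts: diabetes avoided in the early post-transplant period, and acute rejections. Of the second it says "the total number of acute rejections avoided will be used as the measure of effectiveness". It continues: "The incremental cost-effectiveness ratio will be calculated comparing both interventions using the formula", which is the cost difference divided by the effectiveness difference. Robustness "will be assessed through only deterministic sensitivity analyses", carried out one parameter at a time.
- **Health economics analysis** (Discussion) gives the aim as "to investigate the cost-effectiveness of prevention of diabetes with vildagliptin in patients included in the PRODIG clinical trial". Rejection is not part of that aim.
- **Health-related quality of life** says that each patient's "quality-adjusted life year will be calculated, from D0 until M12 or censoring date", using EQ-5D.
- **Health economics analysis** also supports EQ-5D as "recommended by the National Institute for Health Care and Excellence in the UK for the incorporation of health benefits in cost-utility analysis". The use it then describes is different: "The purpose of this secondary analysis will be to assess the association of change in health utility with changes in other variables".

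Elsewhere, acute rejection appears under Study outcomes as a secondary outcome, beside infection, graft loss and death. The trial hypothesis and the sample size concern diabetes only.

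**The concern.** A ratio is informative only if its denominator is clearly away from zero. For diabetes avoided, the protocol plans a large difference. For rejection it states no rate, no direction and no size. If the true difference is zero or small, the observed number of rejections avoided is mostly chance. The ratio could then take a large positive value, a large negative value or no value at all.

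The sensitivity rule makes this harder to see. One-way deterministic analyses vary chosen parameters. They do not show the joint sampling variation of cost and effect, or the probability that the denominator changes sign. A chance difference of one or two rejections could be reported as a firm figure in euros per rejection avoided.

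QALYs, a generic effect measure, are calculated from data already being collected, but they are not among the effectiveness measures named for the ratio.

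**Working it through.** **Inputs from the protocol.** One-year diabetes 40% on placebo and 20% on vildagliptin; two-sided alpha 5%; power 80%; 84 evaluable patients per arm; 186 included; 1:1 allocation (Sample size and power calculation; Randomization).

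**Inputs assumed.** Acute rejection 5%, 10%, 15% or 20%, equal in both arms; an incremental cost of 500 euros per patient for illustration. The protocol gives neither.

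**Step 1: the plan's own figure.** With pooled variance, n per arm = [1.960 × √(2 × 0.30 × 0.70) + 0.842 × √(0.40 × 0.60 + 0.20 × 0.80)]² / 0.20² = (1.270 + 0.532)² / 0.04 ≈ 81.2, so 82 for a fixed design. The stated 84 fits a small group-sequential inflation; fixed-design power at 84 is 0.813. For drop-out, 168/0.90 = 186.7, against 186 stated. The sample size is therefore accepted as given.

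**Step 2: the rejection denominator with no true effect.** Let D be rejections on placebo minus rejections on vildagliptin, each binomial with n = 84. D has mean 0 and SD √(2 × 84 × r × (1 − r)). The probabilities are from the exact distribution of the difference of two binomials.

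| Assumed rate r | SD of D (patients) | P(D > 0) = P(D < 0) | P(D = 0) | P(D within ±2) |
|---|---|---|---|---|
| 5% | 2.8 | 0.43 | 0.14 | 0.63 |
| 10% | 3.9 | 0.45 | 0.10 | 0.48 |
| 15% | 4.6 | 0.46 | 0.09 | 0.41 |
| 20% | 5.2 | 0.46 | 0.08 | 0.37 |

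With all 93 included patients per arm the picture is the same: 0.43 to 0.46 for each sign, and 0.07 to 0.14 for exactly zero.

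**Step 3: the diabetes denominator at the planning rates.** Expected cases avoided = 84 × (0.40 − 0.20) = 16.8; SD = √(84 × (0.24 + 0.16)) = 5.8; P(D > 0) = 0.997. The planning rates are for one year, whereas the economic section counts early post-transplant diabetes, so this is a benchmark and not a forecast.

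**Step 4: a modest real effect on rejection.** With assumed rates of 15% against 12% and 84 per arm, P(D = 0) = 0.077 and P(D < 0) = 0.247. The denominator is zero or negative in about 32% of trials.

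**Step 5: what the ratio would look like.** The ratio is 500 / (D/84) = 42,000/D. With 15% rejection in both arms, the middle 95% of defined ratios runs from −42,000 to +42,000 euros per rejection avoided, that is, out to D = −1 and D = +1. For diabetes at 40% against 20%, it runs from about 1,500 to 7,000 euros per case avoided. The euro values scale with the assumed 500; the contrast in stability does not depend on it.

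**The case against.** **Silence is not an assumption of zero.** A reader might infer that the protocol assumes no effect on rejection, so that the ratio must be noise. The text does not support that. It states no effect, and the justification for choosing vildagliptin describes effects of DPP-4 inhibition on immune cells and cytokines. Those effects are tied to diabetes and not to rejection, but an effect on rejection is not excluded. Secondary outcomes are also commonly left unsized. This stands, so the coin-toss figures are conditional on no true effect.

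**QALYs may be no steadier.** No effect on QALYs is sized either. As an illustration with assumed inputs, a utility loss of 0.05 from diabetes times the planned 20-point reduction gives 0.01 QALY over one year at most. With an SD of 0.15 to 0.20 and 93 per arm, the SE is SD × √(2/93) = 0.022 to 0.029, so the difference has the wrong sign in about 32% to 37% of trials. This stands: exchanging one ratio for another would not cure the instability.

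**The article is condensed.** A reader might infer that no cost-utility result will be produced. The article does not say so; it leaves QALYs out of the named effectiveness measures, and the full plan may add them.

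**Negative ratios.** A reader might also infer that an ambiguous negative ratio will be printed in the hoped-for outcome. The article says only that "The additional cost associated with NODAT could be significantly reduced by efficient prevention". That is not a claim that the strategy saves money overall within one year, and wording on dominance is ordinary reporting detail.

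**One combined measure.** The text speaks of a single measure for the two counts. If they were summed, the diabetes term would steady the denominator, but two unlike outcomes would be added without weights. Two separate ratios is the more natural reading.

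**Conclusion.** The point holds in a limited form. The article affirmatively makes rejections avoided a denominator of the ratio, states no effect on rejection to support it, describes an economic aim that concerns diabetes, and restricts robustness work to methods that cannot show sampling uncertainty or a change of sign.

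If there is no true effect, the sign of the denominator is close to an even split over assumed rejection rates of 5% to 20%, and the ratio is undefined in roughly one trial in seven to one in thirteen. An assumed modest effect reduces the problem without removing it. These results rest on assumed rejection rates, and the euro range rests also on an assumed cost.

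The diabetes ratio does not share this instability at the planning rates, though its sampling uncertainty would also go unreported under the deterministic-only rule. The primary analysis is untouched. This is a cheap improvement to a secondary health-economic analysis.

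**What to change.** 1. Do not form a ratio on acute rejection. Keep rejection as a clinical and safety outcome, and show incremental cost and incremental rejections side by side.
2. Add the QALYs already calculated to the effectiveness measures, adjusted for D0 utility where it is available. The Discussion notes that the ReTransQoL form could not be filled in just before surgery, and the same barrier may affect EQ-5D at D0.
3. Report incremental cost and incremental effect separately, with incremental net monetary benefit over a stated range of willingness to pay.
4. Replace the deterministic-only rule: keep the one-way analyses and add bootstrap or other probabilistic intervals. This is needed for QALYs as well, because their one-year difference may be small and imprecise.

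Cost: changes to the analysis wording and modest extra analysis, with no new data, since costs and EQ-5D are already collected. The cost-per-rejection figure is lost.
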